### Adverse events

Record the time, duration, extent, and treatment of adverse reactions. Evaluate its relevance to treatment.

### Data management

The computer software CDMS is used to establish the corresponding entry procedure and establish a special database system for this trial. Data entry adopts the double entry method, which is completed by two persons independently. Data review uses the verification function in computer software for logical inspection and automatic comparison. After the data is locked, the unit that saves the blind file submits the blind file to the data manager, and the data manager completes the unblinding of the data. The unblinded data is handed over to statistical analysts for analysis. Data that is significantly outside the clinically acceptable range must be verified, and the investigator must provide the necessary explanations.

After the completion of the trial, the informed consent form and the subject’s signature code form will be kept by each hospital. The clinical trial data will be kept until 5 years after the termination of the clinical trial.

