#### Elimination criteria

Patients will be removed from the trial if they meet any of the following criteria:
After selection, the patient is found not to meet the selection criteria or to meet the exclusion criteria.Patients who fail to follow the protocol after selection.Patients with no post-treatment visit records after selection.

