#### Patient shedding criteria

Subjects with poor compliance during the trial, affecting the safety and efficacy evaluation.Subjects with serious adverse events, complications, or specific physiological changes, who are not suitable to continue the trial.Children for whom trial blindness is broken.Children who choose to withdraw from the trial.When combined drugs, especially the drugs that have a greater impact on the effectiveness and safety of the experimental drug.Cases who withdraw from the trial, are lost to follow-up, or who die for before completing treatment.Cases with insufficient data, affecting the evaluation of effectiveness and safety.

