### Statistical analysis

Statistical analysis will be carried out using SAS 9.4 or above. According to the data characteristics, measured data will be analyzed by independent sample *t* tests or rank sum tests for comparison between groups and numerical data will be analyzed by χ^2^or Fisher’s exact probability tests. Laboratory data for all clinical endpoints will be analyzed according to intention to treat (ITT) and compliance (PP) analyses, and safety analysis will be performed using a safety data set (SS). The efficacy scores at the time of patient enrollment, intermediate follow-up (day 3, day 4 to day 7 after treatment), and at the end point of the trial will be calculated, and the mean, standard deviation, median, P5, P75, maximum and minimum values of the differences in values between baseline and the treatment period will be used. PP and ITT will be adopted to analyze the main index and overall index. Subjects with positive urine culture indicators will be included in the statistical subgroup to analyze the correlation between the study program and the overall efficacy evaluation index. Because this is a multicenter, randomized, double-blind controlled trial, the possible central effect on efficacy indicators should be considered.

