#### Blinding

Personnel were blinded to the scale evaluation, data collection, laboratory index testing, and statistics.

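### The Blinding section lists statistics as blinded, but the Data management section unblinds the data before the analysts receive them

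*Protocol article*

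**What the plan says.** Two sections of the protocol article describe who is blind.

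- **Blinding** (under Quality control) is a single sentence: "Personnel were blinded to the scale evaluation, data collection, laboratory index testing, and statistics". It gives no time limit.
- **Data management** sets an order. First, "After the data is locked, the unit that saves the blind file submits the blind file to the data manager". Then "the data manager completes the unblinding of the data". Finally, "The unblinded data is handed over to statistical analysts for analysis".

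Three other sections contain decisions that may need judgement.

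- **Elimination criteria** remove "Patients who fail to follow the protocol after selection".
- **Patient shedding criteria** include "Subjects with poor compliance during the trial, affecting the safety and efficacy evaluation", and also cases whose data are too sparse for evaluation.
- **Statistical analysis** leaves the choice of test to the data: "According to the data characteristics, measured data will be analyzed by independent sample" *t* tests or rank sum tests, with chi-square or "Fisher’s exact probability tests" for count data. The main index is to be analysed in both the intention-to-treat (ITT) and the per-protocol (PP) set.

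**The concern.** A reader of the Blinding section would conclude that the analysis is run without knowledge of the arms. A reader of Data management would conclude the opposite. The trial is presented as double-blind in the abstract and in the Study design section, so the statement should be accurate.

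Blinded analysis protects the decisions that database lock does not freeze. Lock fixes the recorded values. It does not by itself fix whether a child counts as having followed the protocol, whether the data suffice for evaluation, or whether a rate is compared by chi-square or Fisher. If any of these is still open when the analyst knows the arms, it can be settled, even unintentionally, in favour of one arm. The article shows no blinded step at which they are closed.

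**Working it through.** **1. The sections side by side.**

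| Step | Data management | Blinding |
|---|---|---|
| Before lock | Blind file held by a separate unit | Statistics blinded |
| At lock | Blind file passes to the data manager | No time limit given |
| After lock, before analysis | Data manager unblinds | No time limit given |
| Analysis | Analysts hold unblinded data | Statistics blinded |

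The last row is the conflict. If the Blinding sentence is read as blind until lock, the first row agrees, but the word statistics then has almost no content, because the whole analysis comes after unblinding.

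**2. Which decisions could be affected.** Both primary outcomes, antibiotic use rate and clinical cure rate, are proportions. The *t* test or rank sum choice does not touch them; the chi-square or Fisher choice does. Failure to follow the protocol and insufficient data have no stated decision time. Withdrawal and loss to follow-up arise during conduct, while the trial is blind.

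**3. The plan's own sample size, for scale.** Inputs from the Sample size section: 46% against 80%, α = 0.05 (taken as two-sided), and 0.80 read as power. The mean rate is 0.63.

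- Without continuity correction: n = [1.960·√(2·0.63·0.37) + 0.842·√(0.46·0.54 + 0.80·0.20)]² / 0.34² = 30.4, so 31.
- With continuity correction: n = (30.45/4)·[1 + √(1 + 4/(30.45·0.34))]² = 36.1, so 37.

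The stated 37 per group is reproduced with the correction. The point does not rest on it; it only sets the arm size for the illustration.

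**4. Illustration with assumed counts.** Antibiotic users in one herbal arm against control, removing users from the herbal arm only. The uncorrected chi-square equals the pooled test z = (p₂ − p₁) / √[p̄(1 − p̄)(1/n₁ + 1/n₂)].

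| Herbal arm | Control | z | Chi-square p, uncorrected | Chi-square p, corrected | Fisher p |
|---|---|---|---|---|---|
| 21/37 | 28/37 | 0.1892/0.1100 = 1.72 | 0.085 | 0.140 | 0.140 |
| 19/35 (two removed) | 28/37 | 0.2139/0.1123 = 1.90 | 0.057 | 0.097 | 0.083 |
| 18/34 (three removed) | 28/37 | 0.2273/0.1135 = 2.00 | 0.045 | 0.079 | 0.052 |

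Three removals cross 0.05 under uncorrected chi-square only. An analysis that keeps all randomised children stays at 21/37 against 28/37, p = 0.085.

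**5. Test choice alone, assumed counts at the enrolled 40 per arm.** 23/40 against 32/40 gives p = 0.030 by uncorrected chi-square and p = 0.053 by Fisher.

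**6. Where it would not matter.** Close to the planned rates, 17/37 (46%) against 30/37 (81%) gives p = 0.002 by uncorrected chi-square and 0.003 by Fisher. Neither the test nor a few removals would decide the result.

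**The case against.** The strongest defence is that the two sections describe one sequence: everyone, statisticians included, is blind until lock, and the arms are then revealed for analysis. Unblinding after lock is common and acceptable. That part stands, and on this reading the defect lies in the wording. It does not make the Blinding sentence correct as written, because that sentence claims blinded statistics without a time limit and no analysis takes place before the arms are known.

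A reader might go further and infer that the plan settles removals and tests after lock with the arms known. The document does not support this. No section places those decisions after lock. Several removal grounds arise during blinded conduct, and a broken blind is itself a ground for shedding. For the rest the article is silent, and a blind data review with test rules is commonly left to an analysis plan, which is not shown here.

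Nor do the p-values show that three removals would overturn the trial. The counts were chosen near the boundary, and the crossing fails under Fisher and under the corrected chi-square. It arises only in a set that drops those children. Because ITT is planned as well, an ITT result that keeps all randomised children would expose the difference.

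**Conclusion.** The point holds in a limited form. The Blinding section claims a protection for statistics that the Data management section does not provide. This rests on the text alone and needs no calculation.

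The consequence is a possibility, not something the plan prescribes: choices made with allocation known are open unless an unseen analysis plan closes them. Its size cannot be fixed from the document. The illustration shows that with results near the boundary, three removals in a per-protocol set, or the choice between chi-square and Fisher, can change which side of 0.05 the result falls on. At the planned difference they would not. It assumes invented counts, removed children leaving the per-protocol set, and ITT keeping everyone randomised. The article does not spell out those set definitions.

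The correction is worth making because it costs little and makes the blinding statement true.

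**What to change.** **Preferred.** Change the last steps in Data management so that the analysts receive the locked data with the arms coded A, B and C, and the meaning of the codes is released only after the primary analysis is final. The Blinding sentence can then stand.

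**Minimum.** Limit the Blinding sentence to the period before database lock, and add to Data management that membership of the ITT, PP and safety sets, together with the rules for choosing tests, is signed off before the blind file is released. If an analysis plan already provides for this, a reference to it is enough.

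**Cost.** One or two sentences of text and, for the preferred version, one extra hand-over step. No patients and no new data are needed. The downside is that safety review may need an earlier reveal, which should go to someone outside the analysis team.

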### Statistical analysis

Statistical analysis will be carried out using SAS 9.4 or above. According to the data characteristics, measured data will be analyzed by independent sample *t* tests or rank sum tests for comparison between groups and numerical data will be analyzed by χ^2^or Fisher’s exact probability tests. Laboratory data for all clinical endpoints will be analyzed according to intention to treat (ITT) and compliance (PP) analyses, and safety analysis will be performed using a safety data set (SS). The efficacy scores at the time of patient enrollment, intermediate follow-up (day 3, day 4 to day 7 after treatment), and at the end point of the trial will be calculated, and the mean, standard deviation, median, P5, P75, maximum and minimum values of the differences in values between baseline and the treatment period will be used. PP and ITT will be adopted to analyze the main index and overall index. Subjects with positive urine culture indicators will be included in the statistical subgroup to analyze the correlation between the study program and the overall efficacy evaluation index. Because this is a multicenter, randomized, double-blind controlled trial, the possible central effect on efficacy indicators should be considered.

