**Methods:**

This randomized, double-blind, placebo-controlled clinical trial has completed ChiCTR registration. The trial will randomly divide 120 children who meet the inclusion criteria into three groups: experimental group 1 (basic treatment + Gegen Qinlian decoction granules + Erbai drink placebo), experimental group 2 (basic treatment + Erbai drink granules + Gegen Qinlian decoction placebo), and control group (basic treatment + Gegen Qinlian decoction placebo + Erbai drink placebo). The main efficacy indicators will be antibiotic use rate and clinical cure rate, and the secondary efficacy indicators will be time to antibiotic intervention, effective rate, and course of treatment determined after 5 days. The following physical and chemical indicators will be measured: routine blood parameters, procalcitonin, C-reactive protein, electrocardiogram, liver and kidney function, electrolytes, routine urinalysis, routine stool analysis, and stool culture (including drug sensitivity).

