#### Test drugs

Experimental group 1: basic treatment + Gegen Qinlian decoction granules + Erbai drink placebo: Radix Puerariae lobatae (Ge Gen) 10 g, Radix Scutellariae (Huang Qin) 10 g, Rhizoma Coptidis (Huang Lian) 5 g, Radix Glycyrrhizae (Gan Cao) 5 g. (child’s dose, divided into three packets), orally in three times. Placebo (same taste and packaging as Erbai drink granules), children aged ≥ 6 months to ≤r1 year: 3/7 packs/time, three times a day orally; children aged > 1 year to ≤ 3 years: 1/2 pack/time, three times a day orally; children aged > 3 years to ≤ 5 years: 3/4 pack/time, three times a day orally; and children aged > 5 years to ≤ 14 years: 1 pack/time, three times a day orally.Experimental group 2: basic treatment + Erbai drink granules + Gegen Qinlian decoction placebo: Radix Paeoniae Alba (Bai Shao) 10 g, Rhizoma Atractylodis Macrocephalae (Bai Zhu)10 g, Radix scutellariae (Huang Qin) 10 g, Semen Coicis (Yi Yiren ) 10 g, Rhizoma Atractylodis (Cang Zhu) 5 g, Semen Plantaginis (Che Qianzi)10 g (child’s dose, divided into three packs) orally in three times. Placebo (taste and packaging same as Gegen Qinlian decoction granules), children aged ≥ 6 months to ≤ 1 year: 3/7 packs/time, three times a day orally; children aged > 1 year to ≤ 3 years: 1/2 pack/time, three times a day orally; children aged > 3 years to ≤ 5 years: 3/4 pack/time, three times a day orally; and children aged > 5 years to ≤ 14 years: 1 pack/time, three times a day orally.Control group: basic treatment + Erbai drink placebo + Gegen Qinlian decoction placebo: placebo (taste and packaging same as Erbai drink granules and Gegen Qinlian decoction granules), children aged ≥ 6 months to ≤ 1 year old: 3/7 packs/time, three times a day orally; children aged > 1 year to ≤ 3 years: 1/2 pack/time, three times a day orally; children aged > 3 years to ≤ 5 years: 3/4 pack/time, three times a day orally; and children aged > 5 years to ≤ 14 years: 1 pack/time, three times a day orally. Relevant antibiotics (ceftriaxone sodium for injection: 50 mg/kg/day, single intravenous infusion) can be added if required during the course of the illness, if there is an increase in the frequency of stools, a lack of improvement in stool characteristics, fever, increased proportion of neutrophils in the blood, increased CRP or procalcitonin, or increased routine white blood cell count in the stools.

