#### Secondary outcome measures

Time to antibiotic intervention, effectiveness, and treatment course.

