### Quality control

#### Sample size

We calculated the sample size according to our primary study. We found that the use rate of antibiotics in the two groups of patients treated with traditional Chinese medicine was 46% and that of the control group was 80%. Calculate the sample size under the settings of α = 0.05 and β = 0.80. The grouping ratio is 1:1:1. Calculate the single group n = 37, so there are 111 cases in the three groups. Taking into account a drop-out of 10%, In the end, we set the number of cases to 120.

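### The only tests named for measured data do not fit time to antibiotic intervention: on the plan's own rates about 54% of each TCM arm and 20% of controls have no start time

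*Protocol article*

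**What the plan says.** The protocol article lists its secondary outcomes as "Time to antibiotic intervention, effectiveness, and treatment course". The abstract repeats the list: "the secondary efficacy indicators will be time to antibiotic intervention, effective rate, and course of treatment determined after 5 days".

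The Statistical analysis section sorts outcomes into two types. The rule for the first opens with "According to the data characteristics, measured data will be analyzed by independent sample", and the choices it offers are the t test and the rank-sum test. Outcomes of the second type go to chi-square or Fisher's exact tests. No method for event times is named, and nothing says how a child who never starts an antibiotic enters the comparison. The same section calls for intention-to-treat and per-protocol analyses and asks that centre effects be considered.

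Two further places show that many children will have no start time. Under Test drugs, the antibiotic "can be added if required during the course of the illness", so it is conditional. Under Sample size, the use rate in the two groups "treated with traditional Chinese medicine was 46" per cent, and "that of the control group was 80" per cent.

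**The concern.** A time is a measured quantity, so the stated rule points it to the t or rank-sum test. Both need a value for each child, and a child who avoids antibiotics has none. If the tests are run on the times that exist, three things follow.

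- The groups compared are no longer the randomised ones. Membership depends on having needed an antibiotic, which is what the treatment is meant to change.
- The favourable outcome, no antibiotic at all, drops out of the comparison.
- The result depends on which children were spared. If treatment mainly prevents late starts, the remaining starts in the TCM arms are early ones, and TCM appears to bring antibiotics forward.

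The trial is meant to supply evidence on reducing antibiotic use. A secondary result that shows nothing, or points the wrong way, beside a favourable primary result would be hard to interpret.

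**Working it through.** **Inputs.** From Sample size: antibiotic use 0.80 (control) and 0.46 (taken as the rate in each TCM arm), alpha 0.05, 37 per group, 120 in total (40 per arm). From the Interventions section and Table 1: one or two 5-day courses, observation to day 10. The documents give no distribution of start times, so every timing pattern below is an assumption.

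**The plan's own figure.** The stated beta of 0.80 is read as power 0.80, and the test as two-sided. With mean rate 0.63 and difference 0.34:

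n = [1.96·√(2·0.63·0.37) + 0.842·√(0.80·0.20 + 0.46·0.54)]² / 0.34² = 30.4, so 31.

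With continuity correction: (30.4/4)·[1 + √(1 + 4/(30.4·0.34))]² = 36.1, so 37. The planned 37 is reproduced.

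**Children without a start time.**
- Control: 1 − 0.80 = 20%, or 7.4 of 37 (8 of 40).
- Each TCM arm: 1 − 0.46 = 54%, or 20.0 of 37 (21.6 of 40).

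A users-only test at 37 per arm compares about 29.6 controls with 17.0 TCM children.

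**Constant hazards.** The hazard ratio is ln(0.54)/ln(0.20) = 0.383. Over 10 days the hazards are 0.161 (control) and 0.0616 (TCM) per day.
- Mean time among users, 1/λ − 10(1 − F)/F, where F is the use rate: control 6.21 − 2.50 = 3.7 days; TCM 16.23 − 11.74 = 4.5 days.
- Mean antibiotic-free time to day 10 in all children, F/λ: control 5.0 days; TCM 7.5 days.

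The users-only difference keeps its direction but shrinks from 2.5 to 0.8 days. Simulated power at 37 per arm (5,000 replicates):

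| Analysis | Power |
|---|---|
| t test, users only | 15% |
| Rank-sum, users only | 14% |
| Rank-sum, all children, never-users tied at the longest time | about 87% |
| Log-rank, all children | 90% |

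Check on the last row: expected events are 29.6 + 17.0 = 46.6, so the standardised effect is √(46.6/4)·|ln 0.383| = 3.28. Since 3.28 − 1.96 = 1.32, power is about 91%. Even in this benign case the users-only means had the wrong sign in about 18% of trials.

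**Other timing patterns** (40 per arm, 1,000 replicates, same use rates):

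| Pattern | Users-only means, control v TCM | t test significant, users only | Log-rank, all | Rank-sum, all |
|---|---|---|---|---|
| Constant hazards | 3.7 v 4.5 days | 17% | 93% | 91% |
| TCM prevents use at random | 3.7 v 3.7 days | about 5% | 88% | 79% |
| TCM prevents the later starts | 3.7 v 1.7 days | 91%, wrong direction | 63% | 29% |

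In the third pattern the users-only direction was reversed in every simulated trial, although the all-children mean antibiotic-free time favours TCM (5.0 v 6.2 days).

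**Reversal by hand (assumed figures).** Let 40% of both arms start at day 1, with later starts at day 5 in 40% of controls and 6% of TCM children.
- Users only: control (0.40·1 + 0.40·5)/0.80 = 3.0 days; TCM (0.40·1 + 0.06·5)/0.46 = 1.5 days.
- All children to day 10: control 0.4 + 2.0 + 0.20·10 = 4.4 days; TCM 0.4 + 0.3 + 0.54·10 = 6.1 days.

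The users-only comparison favours control; the all-children comparison favours TCM.

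**The case against.** The strongest reply is that the rule is one general sentence, qualified by the characteristics of the data. It neither names this outcome nor restricts it to users, and an unseen analysis plan may settle the matter. That stands as a limit: a reader might infer that the protocol prescribes a users-only comparison, but it does not say so. What remains is that the article does assign a class of method to measured data, and that class has no place for a missing start time unless a scoring rule is added.

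Other stronger readings should also be set aside.

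- **That a rank-sum test cannot use all children.** It can, if never-users share the longest time. Under constant hazards it then comes close to the log-rank test, although it loses more power if TCM prevents late starts.
- **That the result will reverse.** The documents give no timing data. Reversal needs a particular pattern; under constant hazards the effect only shrinks.
- **That treatment course has the same defect.** The article does not define it. It uses the word course for a 5-day block, one or two per child, so the outcome may be a count. No proportion unrecovered at day 10 is given.
- **That daily antibiotic records to day 10 exist for every child.** Table 1 marks days 6 to 10 for drug changes and combined medication as completed only where there is information, and symptoms are recorded until the child leaves the group. Children who recover early may not be observed to day 10.
- **That the main conclusion is at risk.** Antibiotic use rate is a primary outcome, compared as a proportion and not affected by this point.

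**Conclusion.** The point holds for time to antibiotic intervention, as a should-fix. The tests named for measured data, applied to observed times, would leave out about 54% of each TCM arm and 20% of controls and would compare subsets selected by the treatment effect. Under assumed constant hazards and 37 per arm, power falls from about 90% (log-rank, all children) to about 15%; under other assumed patterns the difference disappears or changes sign.

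The 54% and 20% rest on the planning rates. The power figures rest on assumed timing, and the 90% is specific to constant hazards: the log-rank test gave 63% at 40 per arm when only late starts were prevented. The preference for all randomised children does not depend on these figures.

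**What to change.** In the Statistical analysis section, before unblinding, state for time to antibiotic intervention:

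- All randomised children are analysed as time-to-event data: cumulative incidence by arm, a log-rank test stratified by centre and a Cox hazard ratio.
- The observation window is stated, and never-users count as event-free to its end.
- Recovery without an antibiotic ends the risk of the event. It is not treated as non-informative censoring.
- Withdrawals are censored at last contact.
- A rank-sum test on all children, never-users tied at the longest time, is an acceptable alternative.
- The t test on observed times is dropped for this outcome.

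The cost is small: a few sentences of analysis text, standard procedures in the SAS software already planned, and confirmation of the last day on which antibiotic use was recorded for children who leave early. Where that day falls before the end of the window, counting the child as event-free assumes no later antibiotic, and the text should say so.

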### Outcome assessment

#### Primary outcome measures

Antibiotic use rate and clinical cure rate

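### Efficacy scores appear set for an unadjusted comparison of change from baseline; adjusting for baseline score and centre would be at least as precise, a minor gain outside the primary endpoints

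*Protocol article*

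**What the plan says.** All the relevant text is in the Statistical analysis section of the protocol article.

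- **Test for continuous data:** "measured data will be analyzed by independent sample *t* tests or rank sum tests for comparison between groups". No covariate-adjusted model is named.
- **When the score is taken:** "The efficacy scores at the time of patient enrollment, intermediate follow-up (day 3, day 4 to day 7 after treatment") and at the end of the trial. A baseline value therefore exists.
- **Form in which the score is used:** a list of summary statistics (mean, SD, median, percentiles, extremes) of the "differences in values between baseline and the treatment period will be used".
- **Centre:** "the possible central effect on efficacy indicators should be considered", with no method given. Randomization and allocation says that randomisation is stratified by centre.

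The efficacy score is not defined in the article and does not appear among the outcomes. The primary outcomes are "Antibiotic use rate and clinical cure rate". The secondary outcomes are "Time to antibiotic intervention, effectiveness, and treatment course", and the abstract describes effectiveness as a rate.

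**The concern.** Read together, these sentences reduce the efficacy score to a change from baseline and leave only two-sample tests to compare it between arms. A change score does use the baseline, but with its coefficient fixed at 1. When baseline and follow-up are only moderately correlated, that coefficient is too large: the analysis over-corrects, and chance baseline imbalance passes into the estimated effect with the opposite sign. With 120/3 = 40 children per arm, such imbalance is not negligible in a single trial, although it averages out over randomisations.

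What is at stake is precision: wider intervals for the score than the collected data allow. A second, related point is that neither named test, as it stands, has a place for centre, although the plan wants centre considered. One model would serve both purposes.

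**Working it through.** **1. The plan's own figure.** The Sample size section bases the trial on antibiotic use: "treated with traditional Chinese medicine was 46% and that of the control group was 80" per cent, with "Calculate the sample size under the settings of α = 0.05 and β = 0.80". I read the printed β as power and take α as two-sided.

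- Uncorrected: n = [1.960·√(2·0.63·0.37) + 0.842·√(0.46·0.54 + 0.80·0.20)]² / 0.34² = (1.338 + 0.538)² / 0.1156 = 30.4, so 31.
- Continuity-corrected: (30.4/4)·[1 + √(1 + 4/(30.4·0.34))]² = 36.1, so 37.

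The stated 37 per group is reproduced. It rests on a binary endpoint, so nothing below changes it.

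**2. Variance of the two analyses.** Let s0 and s1 be the baseline and follow-up SDs and r their correlation. Per child:

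- Change score: s0² + s1² − 2·r·s0·s1
- Adjusted for baseline (ANCOVA, large sample): s1²·(1 − r²)
- Difference: s0² − 2·r·s0·s1 + r²·s1² = (s0 − r·s1)²

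A square cannot be negative, so apart from a few degrees of freedom the change score is never the more precise. The two are equal when s0 = r·s1.

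**3. Size if s0 = s1 = s (assumed).** The variances become 2(1 − r)s² and (1 − r²)s², with ratio (1 + r)/2. The documents do not give r, so the values below are assumed. The last two columns take 37 per arm.

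| r | Change variance / s² | ANCOVA variance / s² | Ratio | SE ratio | n per arm for ANCOVA to match 37 | ANCOVA power where change has 80% |
|---|---|---|---|---|---|---|
| 0.3 | 1.40 | 0.91 | 0.65 | 0.81 | about 24 | 93.5% |
| 0.5 | 1.00 | 0.75 | 0.75 | 0.87 | about 28 | 90% |
| 0.7 | 0.60 | 0.51 | 0.85 | 0.92 | about 31 | 86% |
| 0.9 | 0.20 | 0.19 | 0.95 | 0.975 | about 35 | 82% |

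Under equal SDs and r below 0.5, 2(1 − r) exceeds 1, so the change score is then less precise than the follow-up score analysed alone.

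**4. Where the excess comes from.** Under equal SDs, a baseline mean difference D between arms shifts the change-score estimate by −(1 − r)·D. With 40 per arm the SD of D is s·√(2/40) = 0.224s. At r = 0.5 the shift therefore has SD 0.5 × 0.224s = 0.112s and variance 0.0125s². That is exactly the gap between the two estimators' variances: 1.00 × 2/40 − 0.75 × 2/40 = 0.0500 − 0.0375 = 0.0125.

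**5. If the SDs differ.** With r = 0.5 and s0 = 0.5·s1, the excess is (0.5 − 0.5)²·s1² = 0: no gain. With r = 0.5 and s0 = 2·s1, the change variance is (4 + 1 − 2)·s1² = 3·s1² against 0.75·s1², a ratio of 0.25. The direction is fixed; the size is not.

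**The case against.** The strongest reply is that the sentence on differences lists descriptive statistics, and no sentence says that these differences are tested. A reader might infer that the protocol prescribes a t or rank-sum test of change scores. It does not say so; that reading comes from joining the sentence to the general rule for continuous data. This part of the objection stands, and the point is worded accordingly.

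Next, covariates for a non-primary score are usual analysis-plan content, and that plan is not shown. This carries less weight, because the article itself names the tests and the form of the variable. A plan that used a baseline-adjusted model would depart from that text, and neither named test as it stands accommodates the centre effect that the same section raises.

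Four stronger readings are tempting and are not supported:

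- **That the baseline is thrown away.** It is used, with slope 1; the fault is inefficiency.
- **That the comparison is biased.** Under randomisation it is not.
- **That a gain of known size holds for any score.** The (1+r)/2 ratio needs equal SDs. Enrolment is limited to mild or moderate illness, while follow-up may mix recovered and unrecovered children, so equal SDs cannot be presumed.
- **That the trial's main result is at risk.** The score is neither defined nor listed as an outcome.

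It is also fair to object that a plain linear ANCOVA may fit badly if the score is ordinal or gathers at its floor as children recover. The fix allows for that.

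**Conclusion.** The point holds as a minor matter of precision. On the natural reading, efficacy scores would be compared as unadjusted changes from baseline. A model with baseline score and centre would do at least as well in large samples, using data that are already collected.

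Under equal SDs, the variance saved is 35%, 25%, 15% or 5% for assumed r of 0.3, 0.5, 0.7 or 0.9. Without equal SDs it could be larger, or close to nothing. These sizes rest entirely on assumed values.

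It corrects no bias, leaves the 37 per group and the final 120 untouched, and has no bearing on the two binary primary endpoints.

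**What to change.** In the Statistical analysis section, state that the follow-up efficacy score will be compared for each herbal arm against control in a model with the baseline score and centre (the randomisation stratum) as covariates. Provide for a rank-based or ordinal version if the score is skewed or piles up at its floor. Keep the change-from-baseline summaries as description. Name in advance the visit at which the comparison is made, so that two contrasts at several visits do not multiply the tests.

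The cost is a sentence or two, standard SAS code, a few degrees of freedom and a check of model fit. No new data are needed.
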